#### Saliva nitrate/nitrite concentrations

Nitrate and nitrite concentrations will be collected via three saliva samples: one before the experimental conditions (time point 0) and at two time points (time points 1 and 2) after the experimental conditions (**Fig 2**). Cotton buds in test tubes will be used to collect the saliva. These samples will be centrifuged and stored at -80°C, until the time of analysis (<6 months from collection). The OxiSelect™ In Vitro Nitric Oxide (Nitrite/Nitrate) Assay Kit (Fluorometric) from Cell Biolabs, Inc. (San Diego, CA, USA) will be used to measure nitrate (NO_3_^-^) and nitrite (NO_2_^-^) levels collected from the saliva samples.

### Data management

All participants will be assigned to a unique identifier number to remain pseudonymous. All data files with personal data will be stored in an encrypted file format and only researchers will have access to the key-coded file. Original paper files will be stored on site and locked in cabinets. Data will be entered electronically on-site in a password-protected file and data will be double checked for errors, with changes being documented. Consistency checks will be carried out for data integrity.

### Sample size

To the best of our knowledge no studies have investigated the acute effects of nitrate consumption on cognitive function nor vascular health in adolescents. Therefore, an adult population was used to calculate effect sizes for the effect of nitrate on these outcomes, however, the adolescent population was used to calculate effect sizes for the effect of breakfast on working memory and psychological outcomes. Arterial stiffness and CBF mechanistic outcomes have less variance than cognitive performance and psychological factors, thus the sample size was calculated from effect sizes of working memory performance and psychological outcomes. Effect sizes were calculated on G*Power software (Franz Faul, Universität Kiel, Germany, v 3.1.9.2) using differences between two dependent means and standard deviations. The sample size was calculated: using α = 0.05, β = 0.8, correlation = 0.5 and assuming a two-tailed test. The effect size based on the effects of nitrate on working memory = 0.63, giving a sample size = 22. The effect size based on the effects of breakfast on psychological factors ranged from 0.67 to 0.48, giving a sample size range between 20 and 36. Our sample size will thus be the largest number found here with seven additional participants to account for 20% drop out rate, thus n = 43.

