**Methods:**

This randomised crossover trial will recruit at least 43 adolescents (13–15 years old). There will be three experimental breakfast conditions: (1) none, (2) low-nitrate (normal breakfast), and (3) high-nitrate (concentrated beetroot juice with normal breakfast). Working memory (n-back tests), CBF (task-related changes in oxygenated and deoxygenated haemoglobin in the prefrontal cortex), and arterial stiffness (pulse wave velocity and augmentation index) will be measured twice, immediately after breakfast and 130 min later. Measures of psychological factors and salivary nitrate/nitrite will be assessed once before the conditions and at two-time points after the conditions.

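### Seven extra participants do not cover a 20% drop-out: 43 enrolled would leave about 34 completers, not the 36 the plan requires

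*Protocol article*

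**What the plan says.** All the inputs are printed in the Sample size section of the protocol article. The calculation rests on paired comparisons, "using differences between two dependent means and standard deviations", with the settings "using α = 0.05, β = 0.8, correlation = 0.5 and assuming a two-tailed test". For the primary outcome, "The effect size based on the effects of nitrate on working memory = 0.63, giving a sample size = 22". For breakfast and psychological factors, the effect sizes "ranged from 0.67 to 0.48, giving a sample size range between 20 and 36".

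The section then chooses the most demanding result: "Our sample size will thus be the largest number found here", which is 36. It enlarges this "with seven additional participants to account for 20% drop out rate, thus n = 43". The Methods paragraph of the abstract repeats the total as a minimum: "This randomised crossover trial will recruit at least 43 adolescents".

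**The concern.** A drop-out rate normally means the fraction of enrolled participants who do not complete. On that meaning, the number to enrol is the number of completers needed divided by the fraction retained. Adding 20% of the completers gives too few, because the loss is then taken from a larger base than the one to which the 20% was applied.

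The recruitment target therefore does not deliver the completers or the power that the same section promises. Readers of the results will judge attrition against the stated 20%. If exactly 20% leave, the trial would have behaved as planned and still report fewer completers than its plan called for. Drop-out is a realistic prospect: each participant attends three laboratory mornings, the Participants section lets them withdraw at any time without giving a reason, and the Discussion expects that some may not drink the beetroot juice.

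**Working it through.** **Inputs (Sample size section).** Two-sided α = 0.05; paired means; correlation 0.5; d = 0.63 (primary, working memory); d = 0.67 to 0.48 (secondary, psychological factors); completers required 36; drop-out 20%; total 43. The power setting is printed as β = 0.8. I read it as power = 0.80, the only reading that reproduces the stated sizes.

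**Step 1: the base sizes.** With n pairs, the paired t-test has n − 1 degrees of freedom and noncentrality d√n. The smallest n with power of at least 0.80 is:

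| d | Plan's n | Recomputed n |
|---|---|---|
| 0.63 | 22 | 22 |
| 0.67 | 20 | 20 |
| 0.48 | 36 | 37 (power at 36 is 79.96%) |

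The last row is a matter of rounding. The effect size is printed to two decimals, and a value of 0.4849, which also prints as 0.48, gives 36. I take 36 as stated.

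**Step 2: how 43 arises.** 36 × (1 + 0.20) = 43.2, rounded down to 43. The seven extra are 7/36 = 19.4% of the completers.

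**Step 3: what 43 delivers at 20% drop-out.** 43 × (1 − 0.20) = 34.4, about 34 completers, two below 36.

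**Step 4: what drop-out 43 can absorb.** (43 − 36)/43 = 7/43 = 16.3%.

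**Step 5: the total that matches 36 and 20%.** 36/(1 − 0.20) = 45, that is nine extra participants. Check: 45 × 0.80 = 36. A total of 44 would give 44 × 0.80 = 35.2, still short.

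**Step 6: effect on power.** Same test as in step 1:

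| Completers | Power, d = 0.48 (secondary) | Power, d = 0.63 (primary) |
|---|---|---|
| 34 | 77.5% | 94.6% |
| 35 | 78.8% | 95.2% |
| 36 | 79.96% | 95.7% |

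The loss at d = 0.48 is 79.96 − 77.5 ≈ 2.4 percentage points.

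**The case against.** Four points can be made for the plan.

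- **The primary outcome is unaffected.** The 36 comes only from the smallest effect in the range for a secondary outcome. Working memory needs 22 by the plan's own figures. This stands, and it limits the importance of the point. It does not remove the error, because the plan chose to size the trial on 36.
- **The difference is tiny.** Two participants and about 2.4 points of power are small beside the uncertainty in effect sizes borrowed from other studies and an assumed correlation of 0.5. This also stands, as a statement about weight.
- **The wording and the analysis leave room.** The abstract's 43 is a floor, so enrolling 45 is permitted. The psychological outcomes will be analysed with linear mixed models, so a participant who leaves after two visits can still inform the contrast between those two conditions, and 34 is a conservative basis for any single contrast. But a floor of 43 does not require 45, and a trial that stops at 43 has met its stated target. The sample size is also built on paired means, and its allowance consists of extra participants, with no reliance on partial data.
- **Adding 20% is common shorthand.** Seven is indeed roughly 20% of 36. That explains where 43 came from, but the sentence says the seven account for the drop-out rate, and they do not.

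**Conclusion.** The statement is wrong as written. A requirement of 36 completers, a 20% drop-out and a total of 43 are mutually inconsistent: 43 covers 16.3% drop-out, and 20% drop-out with 36 completers needs 45. The target is two short.

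If the full 20% is lost, power for d = 0.48 on the psychological outcomes is 77.5%, where the plan aims for 80%. The main question keeps ample power, and no conclusion of the trial is likely to turn on this. It remains a plain arithmetic correction to a published figure.

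The result assumes that drop-out is counted among those enrolled, that only completers contribute (as in the plan's paired calculation), and that the plan's 36 is accepted. Holding strictly to d = 0.48 would give 37 completers and 37/0.8 = 46.25, so 47 enrolled.

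**What to change.** Correct the last sentence of the Sample size section in one of two ways.

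1. **Keep 43.** State that seven extra participants allow for about 16% drop-out. Alternatively, state that 20% drop-out would leave 34 completers, with 77.5% power for d = 0.48 and 94.6% for d = 0.63. This works whatever number has been enrolled, which matters because the Trial status section says recruitment and data collection had already begun.
2. **Keep 20% and 36 completers.** State nine extra participants and a total of 45, and change the minimum in the abstract to match. The present minimum already permits this number.

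Either way, it would help to add that 36 is driven by a secondary outcome and that the primary calculation needs 22, so readers do not take the shortfall to concern working memory. The first option costs one sentence and a slightly less favourable stated power. The second costs two more participants than the present minimum. The design and the analysis stay as they are.

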### Statistical methods

#### Working memory, psychological factors, arterial stiffness, and nitrate/nitrite analysis

Linear mixed effect models, with an unstructured covariance structure, will be used to estimate within condition changes in working memory reaction time and accuracy, psychological factors, arterial stiffness, and nitrate/nitrite concentrations from time point 1 to time point 2 using Stata/SE 17.0 (StataCorp, LLC, Texas, USA). Additional models will be performed with condition and time interactions to assess between condition changes in mean differences in these outcomes.

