#### Part II–Secondary research questions

Is there a statistically significant difference in cognitive task-related CBF (oxy-Hb and deoxy-Hb), arterial stiffness, and psychological measures 130 min after a high-nitrate breakfast compared with a low-nitrate or no breakfast?Is there a statistically significant difference in working memory, cognitive task-related CBF, arterial stiffness, and psychological factors 130 min after having low-nitrate breakfast compared with no breakfast?Will salivary nitrate/nitrite levels differ across breakfast conditions?

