### Experimental conditions

Upon arrival to the laboratory, pre-experimental monitoring measures will be collected (e.g. physical activity and diet diary) and height measured. Participants will arrive at GIH in a taxi (organised by GIH) to be consistent with energy expenditure and physical activity behaviour. Weight will be measured on the day of the high-nitrate breakfast condition. This day was chosen since nitrate provided will be individualised based on body weight. The participants will perform a practice test of the working memory cognitive task, provide a saliva sample (to assess nitrate/nitrite levels), and be asked to answer questions related to psychological factors (mood, alertness, and sleepiness) before the experimental breakfast conditions (**Fig 2**). The three experimental conditions of this study are as follows:

No breakfastLow-nitrate breakfast (regular breakfast)High-nitrate breakfast (regular breakfast supplemented with nitrate provided through concentrated beetroot juice)

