There will be an 80-minute sitting period between the first and second measurements of working memory, cognitive task-related CBF, and arterial stiffness (**Fig 2**). In other words, 130 min from breakfast to the last measurement. The period was determined based on previous research in adults showing that plasma nitrite from beetroot juice peaks at 2.5–3 hrs after ingestion [5]. During the sitting period participants will be able to read books or listen to audio books that can be related to their schoolwork but will not be allowed to use any technological devices nor partake in any physical activity that could lead to arousal. One social break will be provided on each test day, at the same time each test day, whereby the participant can talk to one of the researchers for a duration of 2–3 minutes, which will be consistent for each participant.

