#### Working memory

N-back paradigms will be used to assess working memory performance, consisting of the 1-, 2-, and 3-back tests [51] at two time points (time points 1 and 2) after the breakfast experimental conditions (**Fig 2**). The n-back paradigms are computerised numerical versions where the participants will indicate if the digit presented on the screen is the same digit that was presented 1 digit earlier (1-back), 2 digits earlier (2-back), or 3 digits earlier (3-back) (**Fig 3**). Participants will indicate this via a key press within a 2000 ms period from the onset of the digit, whereby each digit is presented for 1500 ms with an inter-stimuli interval of 500 ms. E-Prime 2.0 (Psychology Software Tools) was used to create the n-back tests and for capturing the data. Before each n-back test, participants will be required to stare at a white dot on a black screen and count from zero to reduce mind-wandering for 20 secs, which will be used as the baseline. Average reaction time (m/s) of correct responses and accuracy (number of correct responses) will be measured for each n-back test across the 3 blocks of 20-digit sequences each, with each n-back test lasting 35 secs.

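### Conditions are compared only on change from a post-meal time point, which does not answer the 130-minute questions or Hypothesis 11

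*Protocol article*

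**What the plan says.** **Analysis.** In Statistical methods, the section covering every outcome except cerebral blood flow (CBF) says "Linear mixed effect models, with an unstructured covariance structure, will be used to estimate within condition changes in working memory reaction time and accuracy", and continues the list with "psychological factors, arterial stiffness, and nitrate/nitrite concentrations from time point 1 to time point 2". The between-condition step is: "Additional models will be performed with condition and time interactions to assess between condition changes in mean differences in these outcomes". The CBF section fits condition and time as fixed effects and then adds their interaction.

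**Timing of time point 1.** The abstract says working memory, CBF and arterial stiffness "will be measured twice, immediately after breakfast and 130 min later". The Working memory section has the n-back tests "at two time points (time points 1 and 2) after the breakfast experimental conditions". The Experimental conditions text adds: "There will be an 80-minute sitting period between the first and second measurements of working memory", and gives 130 min from breakfast to the last measurement.

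**Pre-meal data.** For working memory, the only contact before the meal is a rehearsal that is not named as an outcome: "The participants will perform a practice test of the working memory cognitive task, provide a saliva sample". Psychological factors and saliva do have a pre-meal value (time point 0), but the stated contrast does not use it.

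**Questions and hypotheses.** The primary question names no time point. The secondary questions on CBF, arterial stiffness and psychological measures are set at 130 min, and the breakfast question also includes working memory; it ends "psychological factors 130 min after having low-nitrate breakfast compared with no breakfast". Hypotheses 1–10 are mostly worded as change from time point 1 to time point 2. Hypothesis 11 predicts higher salivary nitrate/nitrite at both post-meal time points.

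**The concern.** In most trials change from the first measurement is change from a pre-treatment value. Here the first measurement already follows the meal, the juice or continued fasting, so subtracting it can remove part of the effect under study. A breakfast effect that appears early and persists would give the same change in every condition and an interaction of zero, although the conditions truly differ at 130 min.

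An early breakfast effect is not far-fetched on the article's own account. The Introduction cites effects of breakfast on energy, satiety, tiredness and alertness, and the Experimental conditions text names postprandial glucose as a possible mediator. A null interaction could then be read as breakfast having no effect, in a study whose abstract points to school-meal policy.

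**Working it through.** **1. The plan's own figures.** The Sample size section uses a difference between two dependent means, two-sided α = 0.05, 80% power and correlation 0.5. A paired t-test with the noncentral t distribution gives:
- d = 0.63: n = 22 (stated 22)
- d = 0.67: n = 20 (stated 20)
- d = 0.48: n = 37 (stated 36, where power is 0.7996)

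So the sample size is reproduced. It describes a simple between-condition difference, not a difference in changes.

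**2. What the interaction estimates.** For conditions A and B, let D1 and D2 be the A-minus-B differences at time points 1 and 2. The planned contrast is D2 − D1. If the 130-minute effect is d and a share f of it is already present at time point 1, the expected value is d − f·d = (1 − f)·d.

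**3. Its precision.** Take SD 1 per measurement, between-day correlation 0.5 and same-day correlation r.
- Var(D2) = 2(1 − 0.5) = 1
- Changes on different days are then uncorrelated (0.5 − 0.5 − 0.5 + 0.5 = 0), so Var(D2 − D1) = 2 × 2(1 − r) = 4(1 − r)
- Standardised effect of the change contrast = d(1 − f) / √[4(1 − r)]

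The divisor is 1.414 at r = 0.5, 1.000 at r = 0.75 and 0.775 at r = 0.85.

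**4. Power with 36 completers, d = 0.48.** The time point 2 contrast has 80%. For the change contrast:

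| Same-day correlation r | f = 0 | f = 0.25 | f = 0.5 | f = 1 |
|---|---|---|---|---|
| 0.5 | 51% | 32% | 17% | 5% |
| 0.75 | 80% | 56% | 29% | 5% |
| 0.85 | 95% | 77% | 44% | 5% |

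Example: r = 0.75 and f = 0.5 gives 0.48 × 0.5 / 1 = 0.24, hence 29%.

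For d = 0.63 the time point 2 contrast has 96%. At f = 0 / 0.25 / 0.5 the change contrast has 74 / 50 / 26% at r = 0.5 and 96 / 79 / 45% at r = 0.75.

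Both f and r are assumptions; the article gives neither. Its 0.5 belongs to the comparison of two dependent means and is not stated for two measurements on one day. The f = 0 column shows precision alone. Moving right along a row shows the effect of subtraction.

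**5. Hypothesis 11.** It predicts raised levels at time points 1 and 2. If the elevation is equal at both, D2 − D1 = 0 although both predictions are true. The stated contrast cannot test it.

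**6. CBF.** The condition main effect in a model without interaction averages over both times, so it is not a 130-minute contrast either.

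**The case against.** The strongest defence is that the analysis matches the hypotheses. Hypothesis 1 predicts improvement from time point 1 to time point 2 that differs between conditions, and the interaction tests exactly that. The primary question fixes no time. A reader might infer that the primary question goes untested or that the primary analysis contradicts it; the article does not support that.

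Second, for nitrate an early reference is a reasoned choice. The article cites a plasma nitrite peak at 2.5–3 h in adults, so little nitrate effect is expected at time point 1, and high- versus low-nitrate is probably little affected.

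Third, it is tempting to say that power falls from 80% to 51% because of the post-meal reference. That fall occurs at f = 0, where nothing is subtracted, and comes only from assuming a same-day correlation of 0.5. Sleep and the previous day's diet and activity are shared within a visit, so a higher value is plausible. At 0.75 the loss vanishes, and above that the change contrast is the more precise of the two.

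Fourth, bias toward zero is not certain. An early effect of opposite sign would inflate the change contrast. The 50 min left for breakfast and testing (130 − 80) is an inference, and the timeline figure is not shown.

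Finally, a condition-by-time model already contains the time point 2 contrast, and an analysis plan not shown might report it.

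All of this narrows the point. It does not remove the mismatch with the 130-minute questions and Hypothesis 11: the article states how between-condition effects are assessed, and that statement answers neither.

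**Conclusion.** The point holds in limited form. As stated, between-condition effects are judged on a difference of two post-meal differences. That tests Hypotheses 1–10 largely as written, but not the secondary questions at 130 min or the level predictions of Hypothesis 11.

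The exposure is mainly in contrasts with no breakfast, including the high-nitrate versus none half of the primary question, and in salivary nitrate/nitrite. The change contrast recovers a fraction 1 − f of the 130-minute effect. If a quarter is present at time point 1, power at d = 0.48 lies between 32% and 77% over the same-day correlations shown, against 80% for the time point 2 contrast. If the whole effect is present, power is 5% whatever the correlation. These figures rest on 36 completers, between-day correlation 0.5 and assumed values of f and r. The d = 0.48 is the article's value for breakfast on psychological factors; for working memory it gives only the nitrate value, 0.63.

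A reader might conclude that Hypotheses 1–10 must be rewritten. They need not be, and data collection began in late February 2022, so rewording prespecified hypotheses would be a substantive change.

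**What to change.** Keep the condition-by-time model and name its contrasts before analysis:

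- Make the between-condition difference at time point 2 the answer to the secondary questions set at 130 min, including CBF. For working memory in the primary question, report it alongside the change-based test of Hypothesis 1.
- Report the time point 1 difference beside it, so that an early effect is visible.
- Test Hypothesis 11 by level contrasts at time point 1 and at time point 2.
- Adjust for time point 0 where it is measured (psychological factors and saliva).
- Keep the hypothesised time point 1 to time point 2 change and its interaction, describe it as further change after the first post-meal test, and do not read a null interaction as absence of a breakfast effect.

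Randomised order makes the conditions comparable at time point 2, so the contrast is valid without subtracting time point 1. It is also the kind of comparison the sample size was computed for.

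Cost: no new data or visits, and one additional contrast to report per comparison. That contrast is less precise than the change contrast if same-day correlation exceeds about 0.75 (with between-day correlation 0.5).

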#### Part II

2. The CBF parameter of oxy-Hb will significantly increase from time point 1 to time point 2 for all breakfast conditions.
This change will be significantly greater for the high-nitrate breakfast condition compared with the low-nitrate and no breakfast conditions.3. Deoxy-Hb will decrease for all conditions from time point 1 to time point 2.
The decrease will be significantly greater for the high-nitrate breakfast compared with the low-nitrate and the no breakfast conditions.4. Arterial stiffness will significantly decrease after the high-nitrate breakfast condition.
The decrease will be significantly greater in the high-nitrate breakfast compared with the low-nitrate and no breakfast conditions.5. Psychological factors (i.e. mood, alertness, and less sleepiness) will improve from time point 1 to time point 2 for the high-nitrate condition
The improvement in psychological factors will be significantly greater for the high-nitrate breakfast compared with the low-nitrate and no breakfast conditions.6. Working memory performance will significantly improve in the low-nitrate breakfast condition from time point 1 to time point 2.
This improvement will be significantly different from the no breakfast condition.7. Oxy-Hb will increase from time point 1 to time point 2 for the low-nitrate breakfast condition.
This increase will be significantly greater for the low-nitrate breakfast compared with the no breakfast condition.8. Deoxy-Hb will significantly decrease for the low-nitrate breakfast condition.
This decrease will be significantly different from the no breakfast condition.9. Arterial stiffness will significantly decrease in the low-nitrate breakfast condition.
This decrease will be significantly different from the no breakfast condition.10. Psychological factors (i.e. mood, alertness, and less sleepiness) will improve from time point 1 to time point 2 for the low-nitrate breakfast condition
This difference will be significantly greater for the low-nitrate breakfast condition compared with the no breakfast condition.11. Salivary nitrate/nitrite levels will be significantly higher after the high-nitrate breakfast at time point 1 and time point 2 compared to the low-nitrate and no breakfast conditions, and higher for low-nitrate vs. no breakfast.

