#### Psychological factors

Psychological factors will be assessed while participants are relaxed and seated and will occur before the experimental conditions (**Fig 2. Time point 0**) and at two subsequent time points (**Fig 2. Time points 1 and 2**). Participants’ mood will be recorded using the Positive and Negative Affect Scale (PANAS) [56]. PANAS has been validated in adolescents and is shown to be a reliable measure of moods [57], with 10 positive and 10 negative moods. Participants will rate their mood on a 5-point scale (very slightly/not at all; a little; moderately; quite a bit; extremely) and will represent how they feel at that moment. The positive affects include: interested, excited, strong, enthusiastic, proud, alert, inspired, determined, attentive, and active; while the negative affects include: distressed, upset, hostile, irritable, scared, jittery, afraid, ashamed, guilty, and nervous. Scores for the positive affects will be added up; providing one overall value and ranging from 10–50 with higher scores indicating higher positive mood. Scores for the negative affects will be added up; providing one overall score and ranging from 10–50 with higher scores indicating more negative mood [56]. Alertness will be measured using a 10 cm visual analogue scale (VAS); ranging from “not at all” to “completely alert” [58]. VAS has previously shown high reliability and validity among adults [59], and also among adolescents [60, 61]. A highly valid measure of sleepiness, the Karolinska Sleepiness Scale questionnaire (KSS) [62, 63], will be used to assess levels of sleepiness via a 9-point Likert scale, ranging from “extremely alert” to “very sleepy, great effort to keep awake, fighting to sleep”; with higher scores indicating higher levels of sleepiness.

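### Hypothesis 11 concerns salivary nitrate/nitrite levels at time points 1 and 2, but the stated analysis compares only the change between those two points and so does not test it

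*Protocol article*

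**What the plan says.** The protocol article asks about saliva in terms of levels. Its secondary research question reads: "Will salivary nitrate/nitrite levels differ across breakfast conditions". Hypothesis 11 (Hypotheses, Part II) makes this specific: "Salivary nitrate/nitrite levels will be significantly higher after the high-nitrate breakfast at time point 1 and time point 2" than in the other two conditions, and "higher for low-nitrate vs. no breakfast".

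Three samples are taken at each visit: "one before the experimental conditions (time point 0) and at two time points (time points 1 and 2) after the experimental conditions" (Saliva nitrate/nitrite concentrations). The Experimental conditions section confirms the pre-breakfast sample: on arrival participants "provide a saliva sample (to assess nitrate/nitrite levels), and be asked to answer questions related to psychological factors".

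Under Statistical methods, nitrate/nitrite is grouped with working memory, psychological factors and arterial stiffness. The linear mixed models are to estimate within-condition changes in these outcomes, including "arterial stiffness, and nitrate/nitrite concentrations from time point 1 to time point 2 using Stata/SE 17.0". Further models with condition and time interactions are then to compare these changes between conditions. No section states a between-condition comparison of salivary levels at either time point, and none gives the time point 0 saliva value a role in the analysis.

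**The concern.** A hypothesis about levels has been paired with an analysis of change whose starting value is post-treatment. By Hypothesis 11 itself, saliva is already raised at time point 1, so subtracting time point 1 removes part or all of the effect the hypothesis describes.

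Saliva is the trial's only biochemical evidence that the juice raised nitrate/nitrite. If working memory shows no effect, readers will look to saliva to tell an ineffective exposure from an exposure that was not achieved. A null or negative interaction could be read as failed exposure when exposure succeeded.

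**Working it through.** **What the stated contrast estimates.** Let L1 and L2 be the differences in mean salivary level between two conditions at time points 1 and 2.

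- Hypothesis 11 claims L1 > 0 and L2 > 0.
- The condition-by-time contrast estimates the difference in change, which is L2 − L1.

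These are different statements:

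- L1 = L2 > 0: the hypothesis is true and the contrast is 0.
- L1 > L2 > 0: the hypothesis is true and the contrast is negative.
- L1 = 0, L2 > 0: the hypothesis is false at time point 1 and the contrast is positive.

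**Illustration of size.** The protocol gives no figure for saliva, so the effects and variances here are assumptions. Inputs: 36 completers (the largest number before the dropout allowance in Sample size; a paired t-test at effect size 0.48 with n = 36 has power 0.7996, so that figure reproduces to rounding); two-sided α = 0.05 (Sample size); SD 1 for every measure; correlation 0.5 between all measures (Sample size uses 0.5 for its own paired comparison; extending it to saliva is an assumption).

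- Level contrast at one time point: variance 2(1 − 0.5) = 1, standard error √(1/36) = 0.167.
- Change contrast: variance 4(1 − 0.5) = 2, standard error √(2/36) = 0.236.

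Simulation, 20,000 runs per row:

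| Rise at time point 1, 2 (SD) | Hypothesis 11 | Change contrast rejects | Level contrasts reject at both points |
|---|---|---|---|
| 1, 1 | true | 5.2% | >99.9% |
| 0.5, 0.5 | true | 5.0% | 69% |
| 2, 1 | true | about 98.5%, true contrast 1 − 2 = −1 | >99.9% |
| 0, 1 | false at time point 1 | 98.5% | 5.1% |

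With equal rises, the change contrast rejects at its type I error rate. In the third row it rejects in the direction that looks like a falling effect. In the last row it rejects although the time point 1 part of the hypothesis is false.

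**What time point 0 could add.** Assume between-day correlation 0.5 and same-day correlation r. The time point 2 level contrast has variance 1 unadjusted and 1 − [2(r − 0.5)]² when adjusted for the time point 0 difference. For r = 0.5, 0.7 and 0.8 this is 1.00, 0.84 and 0.64. The square roots are 1.00, 0.92 and 0.80, so the standard error falls by 0%, 8% and 20%. The values of r are assumed.

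**The case against.** **The model already contains the answer.** A mixed model with condition, time and their interaction includes the condition difference at each time point, so Hypothesis 11 could be tested by post-estimation contrasts from the same fit. This stands, and it makes the repair easy. It does not remove the point: the methods section does more than stay silent on detail, because it says what the models are for, and that purpose is change and differences in change.

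**Equal rises are a special case.** This also stands. Time point 1 is immediately after breakfast and time point 2 is 130 minutes later, timed with reference to a later plasma nitrite peak. No document figure supports equality, so a reader should not infer that the saliva analysis will probably be null. But a growing difference, while giving a positive interaction, still says nothing about the claim at time point 1.

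**Saliva is not the only record of exposure.** Correct. Juice comes from one batch with stated content, and the amount drunk is recorded if it is not finished. Saliva is the only biochemical check.

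**Does the same fault affect mood, alertness and sleepiness?** A reader might infer this, since these scales are also measured at time point 0: "Psychological factors will be assessed while participants are relaxed and seated and will occur before the experimental conditions". The documents do not support it. Hypotheses 5 and 10 are themselves framed as change from time point 1 to time point 2, and the stated analysis matches them. Nor does omitting time point 0 leave visit-level differences in the error of that change. With the covariances used above, the covariance of the time point 0 difference with the change contrast is 2(r − 0.5) − 2(r − 0.5) = 0. What remains is narrower: the change contrast subtracts any breakfast effect already present at time point 1.

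**Time point 0 may be used without being listed.** Possible. The methods section names no covariates, although the pre-experimental monitoring section commits to adjusting for activity, sedentary time and sleep. The absence of a stated role is therefore a secondary part of this point.

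**Conclusion.** The point holds for saliva. The stated analysis estimates L2 − L1, while Hypothesis 11 is about L1 and L2 separately. The contrast can be null or negative when the hypothesis is true, and significant when it is false at time point 1. This conclusion is algebraic and needs no assumption. The rejection rates rest on assumed SDs, correlations and effects, and show the direction of the problem rather than predicting this trial's result.

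The consequence is limited to a secondary outcome. Working memory, for which no time point 0 outcome measurement is planned, is untouched, and so is the sample size. For the psychological scales there is no mismatch between hypothesis and analysis.

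**What to change.** For saliva, state that Hypothesis 11 is tested by the condition contrasts at time point 1 and at time point 2 from the condition-by-time mixed model, with that visit's time point 0 value as covariate. Name the three pairs (high-nitrate vs low-nitrate, high-nitrate vs none, low-nitrate vs none). The hypothesis does not repeat the time points for the last pair, so say that both apply if that is meant. The time point 1 to 2 change can stay as a description of the time course.

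For mood, alertness and sleepiness, keep the planned change analysis for Hypotheses 5 and 10. Condition differences at time points 1 and 2, adjusted for time point 0, may be added as a supplementary analysis to show any immediate breakfast effect.

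The cost is analysis wording only. All three samples and questionnaires are already in the schedule, and no new data are needed.
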